### Interim analyses {21b}

No interim analysis is planned in accordance with the section {20a}.

### Methods for additional analyses (e.g. subgroup analyses) {20b}

Regressions will be adjusted for various characteristics related to beverage consumption in children and parents, and differences between schools at randomisation. Adjustment variables will be chosen based on the differences observed between the randomised groups at inclusion. Stratified analyses are planned based on the inclusion characteristics already chosen: child body weight status, family socio-economic status, and some school indicators such as SSEI and province. Purposely, a predefined and limited number of stratified analyses will be undertaken, and repetition of analysis will be corrected for.

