### Objectives {7}

The first objective of the DRINK trial is to evaluate the long-term effectiveness of nutrition- and sustainability-based interventions on the reduction in SB intake and on the increase in tap water consumption in 3rd to 6th grade children (8 to 11 years of age).

The secondary objectives are (i) to specifically study the potential interaction between nutrition- and sustainability-based information provided within the interventions, (ii) to identify individual and family moderators of the intervention effectiveness, (iii) to assess school staff adherence to the set of interventions and to identify obstacles in the implementation of the interventions, and (iv) to estimate the total cost of the interventions in order to plan their generalisation.

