### Outcomes {12}

The first quantitative judgement criterion will be the change over time in the mean SB consumption (in ml/day) in the intervention groups compared with the control group (Fig. 1). The secondary criteria of judgement will be the change in the proportion of children consuming SB each day on the one hand and in the mean consumption of water (in ml/day) on the other hand. Quantitative outcomes in ml/day will be evaluated through a 4-day booklet, while the daily consumption will be based on a short frequency questionnaire. These outcomes will be measured at the second wave of data collection and changes estimated by difference with the pre-intervention measurements. Findings at the first post-intervention data collection will also be presented once the trial is finished.

Among the secondary objectives of the DRINK trial, the same outcomes will be used to assess the potential interaction between nutrition- and sustainability-based interventions (Fig. 1). The other three secondary objectives will be assessed using complementary information as described below. Altogether, the information collected and the regular monitoring of the trial development (including cost which is one of the objectives) will also enable to develop a comprehensive process evaluation.

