### Sample size {14}

The sample size determination is based on the cluster-randomised factorial plan [45, 46]. The following assumptions have been set for the first criterion of judgement: (i) observed mean of SB consumption, i.e. 200 ml/day (SD: 120 ml) [47]; (ii) a 15% reduction in the intervention group (either nutrition or sustainability), i.e. mean 170 ml/day at the last 2-year follow-up and stability in the control group; (iii) type I error (alpha) of 5%; (iv) statistical power of 80%; and (v) intra-class correlation of 0.08 (estimation based on the “Health Behaviour in School-aged Children” (HBSC) survey carried out in 2018 in French-speaking Belgian primary schools) [48]. The theoretical total number of schools needed is estimated at 48, corresponding to around 3200 students surveyed during the 2 years (based on the same 2018 HBSC survey: on average, four classes in each participating school and 17 students in each of these classes). Since we use a factorial plan, 12 schools are allocated in each group (Fig. 1).

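### The objective is to identify moderators, but the only stated method is stratified analysis; no group-by-moderator interaction test is stated

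*Protocol article*

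**What the plan says.** Section {7} of the protocol article gives as secondary objective (ii) "to identify individual and family moderators of the intervention effectiveness". Section {12} says that the secondary objectives other than the factorial interaction will be assessed with information described later in the article.

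The only later text on method that matches objective (ii) is in section {20b}: "Stratified analyses are planned based on the inclusion characteristics already chosen: child body weight status, family socio-economic status". School-level characteristics, among them the SSEI and the province, are listed as well. The same section adds that "a predefined and limited number of stratified analyses will be undertaken, and repetition of analysis will be corrected for".

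The article speaks of interaction only for the two intervention types. Section {12} says that "the same outcomes will be used to assess the potential interaction between nutrition- and sustainability-based interventions", and sections {6b} and {7} use the word in the same sense. No intervention-by-characteristic term or heterogeneity test is stated anywhere.

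**The concern.** A moderator is a characteristic across whose levels the effect differs, so identifying one needs an estimate and a test of that difference. A stratified analysis gives one effect estimate and one test per stratum, each against zero. Two strata with the same true effect can easily fall on opposite sides of the significance threshold, because each is less precise than the whole trial.

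The planned correction limits false positive findings within strata. It does not turn several tests against zero into a test of whether the effects differ.

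If moderators were read off the stratum results, the trial could report that an intervention works in one kind of child or school and not in another when the effect is the same in both. The dissemination plan takes the findings to decision-makers for health promotion at school, with generalisation in view, so such a contrast could influence whom the programme is offered to.

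**Working it through.** **Inputs** (section {14} unless noted). Mean 200 ml/day, SD 120, reduction to 170, so the effect is 30 ml/day. Alpha 5% (taken as two-sided), power 80%, ICC 0.08. Cluster size 4 × 17 = 68. Twelve schools per group, hence 24 versus 24 schools for each factor (section {6b}). SSEI is used in tertiles (section {15}).

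**The plan's own figure.** Unclustered n per pooled arm = 2 × (1.96 + 0.84)² × (120/30)², which gives 252. Design effect = 1 + 67 × 0.08 = 6.36. Then 252 × 6.36 = 1603 per arm, 3205 in total, and 1603/68 = 23.6, so 24 schools per arm and 48 in all. This matches the stated 48 schools and about 3200 pupils. Overall power at 24 versus 24 is 0.81.

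**Child-level characteristic, same true 30 ml effect in both strata.** With m pupils per school in a stratum, the SE of the stratum effect is sqrt[(2/24) × 14400 × (0.08 + 0.92/m)]. Both strata come from the same schools, so their estimates share the school component and are correlated.

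| Split | m per school | SE (ml) | Power per stratum | Strata disagree in significance |
|---|---|---|---|---|
| 50/50 | 34 and 34 | 11.3 and 11.3 | 0.75 and 0.75 | 18% |
| 20/80 | 13.6 and 54.4 | 13.3 and 10.8 | 0.61 and 0.79 | 27% |

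The disagreement rates come from simulation (400,000 draws). For the 50/50 split a direct bivariate normal calculation agrees: the correlation is 0.08/(0.08 + 0.92/34) = 0.75, both strata are significant in 66% of trials, and 0.754 + 0.754 − 2 × 0.6635 = 0.18.

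Under the same conditions an interaction test at 5% declared moderation in 5.0% of simulated trials.

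**SSEI tertiles, about 8 versus 8 schools in each, same 30 ml effect.** SE = sqrt[(2/8) × 14400 × (0.08 + 0.92/68)] = 18.35, z = 30/18.35 = 1.63, power p = 0.373. Tertiles contain different schools and are independent, so P(not all three agree) = 1 − p³ − (1 − p)³ = 1 − 0.052 − 0.247 = 0.70. With Bonferroni for three tests (alpha 0.0167), p = 0.224 and the result is 0.52.

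**Effect of the correction on child-level strata.** If the correction were Bonferroni over four characteristics (assumed; alpha 0.0125), disagreement would rise from 18% to 23% (50/50) and from 27% to 31% (20/80), because power within strata falls. The interaction test would err in 1.25%.

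**No true effect anywhere.** At the 5% level disagreement is about 6% to 7% for a child-level characteristic and 1 − 0.95³ − 0.05³ = 14% for tertiles.

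**SE of the difference between two child-level strata (50/50).** The school component cancels, so SE = sqrt[(2/24) × 14400 × 0.92 × (2/34)] = 8.1 ml (no random slope for the moderator). Treating the two stratum estimates as independent gives sqrt(2) × 11.33 = 16.0 ml, about twice the actual value.

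**The case against.** The strongest reply is that this is a condensed article and no analysis plan is shown. Section {20b} does not exclude an interaction test and does not say how moderation will be declared; a reader might infer that interaction terms have been rejected and that moderators will be named by comparing significance. The text does not support that: it says only that stratified analyses are planned. It also does several things properly: the characteristics are already chosen, their number is limited, and repetition is corrected for. What remains is that the article is not silent on method. It names one, attaches the multiplicity correction to it, and that method does not answer objective (ii).

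A second reply is that the largest figure belongs to SSEI, a school indicator, whereas objective (ii) concerns individual and family moderators. That stands. For child and family characteristics the relevant range is 18% to 27%. The 70% also needs roughly equal numbers of schools per arm in each tertile, and section {16a} describes allocation by simple division into four groups, without stratification by SSEI.

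A third point concerns precision. A reader might infer that splitting the sample by a child-level characteristic doubles the SE of the effect difference, from about 8 to about 16 ml. It does not: with balanced strata from the same schools, the difference between the two separate estimates also has an SE of about 8 ml. The 16 ml arises only if someone ignores the shared schools, a step the article does not propose. It is a pitfall to avoid, not a loss built into the plan.

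**Conclusion.** The point holds in this form: the stated method for the moderator objective does not test moderation, and the stated correction does not repair that. With a uniform 30 ml effect, stratum verdicts would conflict in about 18% to 27% of trials for child-level characteristics, roughly four to five times the 5% of an interaction test. For SSEI tertiles they would conflict in about 70% (52% after Bonferroni for three tests).

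These figures rest on assumed split sizes, on the planning SD and ICC applying to the analysed outcome, on no attrition, and on a normal approximation. They presume a real effect; without one the conflict rates are lower.

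The primary effectiveness analysis is not affected. This is a weakness in a secondary objective, worth correcting before the data are analysed.

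**What to change.** In section {20b}, or in the analysis plan that carries it out, state that each pre-chosen moderator is tested by a group-by-moderator term in the full-sample multilevel model already planned in section {20a}. Apply the multiplicity correction to those interaction tests. Report stratum-specific estimates with confidence intervals from the same model, as description only. This keeps the shared schools in the calculation, so the SE of the difference is right for child-level characteristics.

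The cost is a change of wording; no further data are needed.

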### Methods in analysis to handle protocol non-adherence and any statistical methods to handle missing data {20c}

Adherence to the intervention will be described based on the school audits at times 2 and 3, to better understand the findings, but will not be taken into account in the analyses of effectiveness. In addition, missing information for children and parents will be addressed through sensitivity analysis by using adapted statistical methods such as a two-stage targeted minimum loss-based estimator [61].

### Plans to give access to the full protocol, participant-level data, and statistical code {31c}

The protocol registered will be updated and made available under request for documents which are not available on the ISRCTN website. Intervention documents, information letters and questionnaires are available upon request. Furthermore, the ULB is currently developing a plan for data deposition of research for the coming years; we will follow the institutional recommendations as soon as rules, procedures, and security are established. In the meantime, databases will be stored and protected in the cloud of the ULB IT system, and statistical coding will be made available if requested by reviewers for instance. Scientific collaboration will be welcomed once the main objectives have been analysed.

## Oversight and monitoring

### Composition of the coordinating centre and trial steering committee {5d}

The coordinating centre comprises the principal investigator, a project leader and a part-time researcher who are supported by the paediatric dietitians and administrative/logistic staff. Regular meetings are organised to follow up the study progress and schools’ participation, to plan the next steps for intervention implementation and data collection, and to address any question related to data quality.

An international scientific committee has been established to support the development of the protocol, data collection, and intervention content and to follow the progress of the research. It is made up of epidemiologists, psychologists, public health researchers, and one economist, all having previous experience in one or several fields covered in the DRINK project (see the “Acknowledgments” section). Three meetings were organised before the beginning of the project, and yearly meetings are planned during the whole length of the project. In addition, a steering committee gathers stakeholders and education authorities in Belgium. It is informed about the progress of the research and may give feedback on the general context, but members do not interfere with the scientific content of the research.

### Composition of the data monitoring committee, its role, and reporting structure {21a}

Considering no specific harmful effect is expected to lead to the trial stopping, a data safety monitoring board has not been considered as necessary.

### Adverse event reporting and harms {22}

No adverse event or harmful effect even minor is anticipated.

### Frequency and plans for auditing trial conduct {23}

During the protocol preparation (2020–2021), the Scientific committee met three times. Since then, the meetings occur once a year. The steering committee also meets once a year. For both committees, a comprehensive update of the trial is presented, and any concern is fully addressed. The research team meets every 2 weeks to discuss the progress of the trial as well as any issues that may occur.

### Plans for communicating important protocol amendments to relevant parties (e.g. trial participants, ethical committees) {25}

Substantial amendments to the protocol will be notified to the Ethical Committee and the International Scientific Committee for approbation (for instance, the split into two cohorts (see the section {13}) has been approved by the Scientific Committee). If amendments would affect children, parents, and school staff, they will also be informed. Non-substantial amendments will not be communicated but related changes will be documented and detailed in the further publications.

## Dissemination plans {31a}

Dissemination of results will include several components. Obviously, we will present our findings in various peer-reviewed journals (following the CONSORT extension for cluster randomised trials) and at international conferences. Recommendations from the International Committee of Medical Journal Editors will be followed to define authorship eligibility and order. Furthermore, our regional involvement in health promotion programmes in Brussels and Wallonia will be used to extend the result dissemination to various stakeholders and actors of the field in these domains (education staff, health promotion at school, nutrition, environment). The staff at the participating schools will be invited to a specific presentation of the results. This will be an opportunity to collect their final feedback on all the components of our research. Finally, our research has been developed so that interventions could be generalised. Therefore, we will present our findings, whether positive, null, or negative, to the decision-makers of health promotion at school (including the Ministry of Health, FWB). Indeed, beyond our own research, the evaluation of health promotion interventions needs to be developed, independently of the topics addressed.

## Discussion

Careful evaluation of health promotion at school is crucial. Indeed, school is identified as an interesting health-related intervention setting, but efficiency of health promotion at school has not been sufficiently evaluated so far. Several systematic reviews underlined the methodological limitations of the relatively few published studies. Previous studies lacked several methodological components, that will be addressed in the DRINK protocol. For instance, the theoretical sample size leads to a number of schools much higher than what has often been published, not due to an expected small effect size, but because it has been computed by taking into account the cluster design. Another strength is the long-term evaluation. On the one hand, it will enable to measure the behavioural changes that are expected to last for a long time. On the other hand, the long-term follow-up may decrease school participation and increase the children’s contamination if some of them change schools during the trial. This is why we have measured the burden of intervention and of data collection. However, the school staff must still organise the distribution of the documents and keep the list of correspondence between the names and ID numbers.

Multiform interventions aimed at being included in the daily life of schools have purposely been adapted to the school context. Long-term school adherence is a key component of such interventions, while staff are frequently requested either for research projects or for the inclusion of actions beyond their main attributions. Therefore, interventions are not fully standardised between schools of a given group, but at the same time, such an adaptation leads to a more realistic implementation. Indeed, when the research was developed, concern for a future generalisation was kept in mind continuously. As mentioned in the “Introduction” section, the originality of our research lies in the factorial randomisation plan aiming at evaluating the effectiveness of two series of promoters towards a healthy diet; health and nutrition, environmental sustainability, or combined. This research protocol and its further findings will open new opportunities for research in health promotion, especially regarding dietary behaviours.

The measurement tools (questionnaires and 4-day booklets) have also been carefully developed leading to a comprehensive evaluation of the expected effectiveness of interventions. The 4-day booklet, including coloured stickers, is really appreciated by children so far, and the calibration study will enable the measure of error against a 24-h recall made by trained dietitians. Given the age of the children, it is necessary to ask parents to answer some questions through a questionnaire in addition to theirs (Table 2). Though this complexifies the data collection, measuring their attitude toward beverages will complete the assessment of familial facilitators and barriers in the children’s dietary behaviour changes. A similar purpose is addressed through the interview of the school staff: information collected will inform the feasibility of future generalisation. Despite regular contacts made by the research team, the main concern is the willingness of school staff to organise the data collection, especially in the control group. The completion rate of questionnaires and 4-day booklets is expected to be lower than if research interviews had been undertaken; however, this method is too costly in the frame of our grants. Lastly, the COVID-19 pandemic has widely affected schools and their staff, making the implementation of such research projects in 2021 and 2022 difficult. School participation rate will therefore be underestimated compared to more usual conditions.

Developing and evaluating health promotion actions related to healthy and sustainable diet offer important perspectives for public health. To date, combining and assessing the possible interaction between nutrition-based and sustainability-based interventions has not been studied yet. Our research will provide an original and topical insight of health promotion at school around dietary behaviours. The dissemination plan will enable to widely inform stakeholders, school staff, and families, in addition to the scientific community through the usual medium (articles, conferences), about the research findings in 2023–2025.

## Trial status

The first wave of data collection took place in Spring and Autumn 2021, and the second wave was just finished at the beginning of 2023. The third and last wave of data collection is planned for the period from April to December 2023. The main results will be disseminated by the end of 2024, through publications and conference communications.

## Data Availability

Data collected in the frame of the DRINK trial will be made available in the future for collaborative research questions once the main objectives have been analysed.

## Abbreviations

cRCT: Cluster randomised controlled trial
DRINK: Decreasing consumption of sugar-sweetened beverages and Raising tap water consumption through Interventions based on Nutrition and sustainability for Kids
ESP: *Ecole** de Santé **Publique* (School of Public Health)
FWB: Federation of Wallonia-Brussels
HBSC: Health Behaviour in School-aged Children
SB: Sweetened beverages
SSEI: School socio-economic index
TPB: Theory of planned behaviour
ULB: *Université libre de Bruxelles*
